# Investigating the safety and activity of the use of BTT1023 (Timolumab), in the treatment of patients with primary sclerosing cholangitis (BUTEO): A single-arm, two-stage, open-label, multi-centre, phase II clinical trial protocol

**DOI:** 10.1136/bmjopen-2016-015081

**Published:** 2017-07-03

**Keywords:** Immunology, Hepatobiliary Disease, Immunology, Hepatology, Clinical Trials

## Abstract

**Introduction:**

Primary sclerosing cholangitis (PSC) is a progressive inflammatory liver disease characterised by relentless liver fibrosis and a high unmet need for new therapies. Preventing fibrosis represents an important area of interest in the development of vital new drugs. Vascular adhesion protein-1 (VAP-1) drives inflammation in liver disease, and provision of an antibody against VAP-1 blunts fibrosis in murine models of liver injury.

**Methods and analysis:**

BUTEO is a single-arm, two-stage, open-label, multi-centre, phase II clinical trial. Up to 59 patients will receive treatment with anti-VAP monoclonal antibody, BTT1023, over a 78-day treatment period. Adults with PSC and a serum alkaline phosphatase (ALP) of at least 1.5 times the upper limit of normal will be included. Our primary outcome measure is a reduction in ALP by >25% from baseline to Day 99. Secondary outcome measures include safety and tolerability, changes pre therapy/post therapy in circulating serum VAP-1 as well as imaging findings. The first patient participant was recruited on 08 September 2015.

**Ethics and dissemination:**

This protocol has been approved by the Research Ethics Committee (REC, reference 14/EM/1272). The first REC approval date was 06 January 2015 with three subsequent approved amendments. This article refers to protocol V3.0, dated 16 March 2016. Results will be disseminated via peer-reviewed publication and presentation at international conferences.

**Trial registration:**

The trial is registered with the European Medicines agency (EudraCT: 2014-002393-37), the National Institute for Health Research (Portfolio ID: 18051) and ISRCTN: 11233255. The clinicaltrials.gov identifier is NCT02239211. Pre-results.

Strengths and limitations of this studyUnique, tailor-made clinical trial design incorporating a dose confirmatory and safety stage (based on the traditional 3+3 design), then followed by a phase II Simon’s two-stage design.Brings the translation of laboratory research into a proof of activity clinical trial.An early-phase experimental medicine study of a novel first-in-class drug, in a chronic disease cohort with a large unmet need for new therapies.Aims to address not just the need for new therapies but also the need for reliable clinical trial endpoints as well as biomarkers for staging and predicting clinical outcomes.Small cohort due to primary sclerosing cholangitis being a rare orphan disease as well as unpredictability of the disease making stability for clinical trial inclusion difficult.Short duration of the treatment period in which goal is to demonstrate collective markers of efficacy to justify longer and placebo-controlled trials.Limited evidence base for the primary endpoint of a reduction in alkaline phosphatase in the context of anti-fibrotic agents, however accepting that there is no alternative surrogate currently available.Translational study from mice into human subjects and the unknown differences this may entail.

## Introduction

End-stage liver disease, regardless of aetiology, is characterised by progressive hepatic fibrosis culminating in liver cirrhosis and accompanying increased risks of liver cancer, liver failure, portal hypertension and death. Preventing progressive liver fibrosis represents an important area of interest in the development of new drugs suitable for all patients with liver disease. Primary sclerosing cholangitis (PSC) is a prime example of a progressive inflammatory liver disease which is characterised by persistent liver fibrosis and a high unmet need for new therapies. PSC has a population incidence of 1.3 per 100 000 annually, with a prevalence of 16.2 per 100 000.^1^
^2^
^3^ It affects both men and women, with a median age of 41 years,^4^ and is associated with inflammatory bowel disease (IBD) in 80% of cases.^5^ More than 50% of patients require liver transplantation within 10–15 years of symptomatic presentation,^6^
^7^ reflecting the failure of medical therapies to have any impact on the clinical outcome: in the UK, for example, PSC is now the leading autoimmune liver disease indication for transplant, despite being the rarest of the autoimmune liver diseases. One barrier to the development of efficacious new medical therapies is the lack of clinically relevant endpoints and there is an urgent need to develop appropriate non-invasive surrogate endpoints to improve clinical trial design.^8^

### Vascular adhesion protein-1 (VAP-1)

Vascular adhesion protein-1 (VAP-1) is a 170-kDa homodimeric type 2 transmembrane sialoglycoprotein with a short cytoplasmic tail of no known signal sequence, a single transmembrane segment and a large extracellular domain. VAP-1 is constitutively expressed on human hepatic endothelium and supports lymphocyte adhesion and transendothelial migration. Cloning of VAP-1 revealed it to be a copper-dependent semicarbazide-sensitive amine oxidase (SSAO) which catalyses the oxidative deamination of exogenous and endogenous primary amines resulting in the generation of aldehyde, ammonia and H_2_O_2_. These products activate NFκB-dependent chemokine secretion and adhesion molecule expression in liver endothelium and may initiate and propagate oxidative stress following the conversion of H_2_O_2_ to hydroxyl free radicals. A soluble form of VAP-1 (sVAP-1) accounts for nearly all of the circulating amine oxidase activity in humans. 9

The progression of PSC to scarring, cirrhosis and hepatobiliary cancer is driven by a chronic inflammatory response and immune cell mediated destruction of bile ducts.^10^ Our research implicates VAP-1 in the inflammation that drives fibrogenesis in liver disease.^11^ VAP-1 also acts as an adhesion receptor to support leucocyte recruitment in liver inflammation, a function that is critical in animal models in the formation of fibrosis.^12^ Thus, inhibition of VAP-1 is expected to impact both inflammation and fibrosis; indeed, treatment with an antibody against VAP-1 prevents fibrosis in murine models of liver injury.^9^ Data also shows particularly high levels of circulating serum VAP-1 (sVAP-1) in patients with PSC as well as a strong correlation between sVAP-1/SSAO activity in serum and histological fibrosis scores in patients with fatty liver disease.^9^ Based on the strong up-regulation of hepatic VAP-1 reported in PSC patients,^9^ we hypothesise that levels of sVAP-1/SSAO will correlate with the severity of fibrosis in PSC and will predict patients at risk of progressive disease.

These observations underpin our proposal that VAP-1 has an important role in the progression of liver fibrosis. We now plan to test the hypothesis that inhibiting VAP-1 with a neutralising antibody (BTT1023) will reverse or delay fibrogenesis in patients with PSC. Additionally, reliable biomarkers that correlate with fibrosis stage and progression of liver disease are in demand in order to predict outcome and to stage disease, without the need for invasive liver biopsy. This research will allow us to translate laboratory research into a proof of activity clinical trial that will elucidate the role of VAP-1 in liver fibrosis and its potential as a therapeutic target and biomarker.

### BTT1023 (now known as Timolumab)

BTT1023 is a fully human, monoclonal, anti-VAP-1 antibody which blocks the adhesion function of VAP-1, thereby diminishing leucocyte entry into sites of tissue inflammation. Going forward, BTT1023 will be known as Timolumab; however, the original numeric name is used in this manuscript in order to remain in keeping with the trial protocol. In vivo, blocking VAP-1 function with an anti-mouse anti-VAP-1 antibody significantly alleviates inflammation in mouse models of arthritis and liver fibrosis.^13^ BTT1023 appears to be safe and well tolerated in humans: BTT1023 has been given in doses up to 8 mg/kg in patients with rheumatoid arthritis and psoriasis after oral premedication (cetirizine and ibuprofen) and also appears safe and well tolerated in repeated intravenous dosing.^14^ No cytokine release syndrome was seen. This dose therefore appears reasonable as a starting point and is considered to provide appropriate bridging into existing clinical data.

In the well-tolerated arthritis study, patients received 5 doses at fortnightly intervals with potentially efficacious trough levels being achieved by Day 42, after 3 doses. The psoriasis study used a more rapid loading of 3 doses at Days 1, 8 and 22, which was also well tolerated. Therefore, we have decided to deploy the accelerated dosing scheme (ie, dosing on Days 1 and 8 and biweekly thereafter) in the current study.^14^

BTT1023 is produced in a Chinese hamster ovary cell culture and purified with appropriate methods including specific viral inactivation and removal procedures. BTT1023 is contained in single-use 100 mg/10 mL glass vials and requires dilution with BTT1023 IV Infusion Diluent (0.9% sodium chloride and 0.02% polysorbate 80 in water for injection) prior to administration by intravenous infusion. The amount of diluent to be added to the BTT1023 concentrate is calculated to consistently provide a total diluted drug product infusion volume of 50 mL. BTT1023 and its diluent are stored at 2–8°C and the maximum shelf life for the diluted infusion solution is 24 hours when stored at this temperature.

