## Methods

### Study design overview

BUTEO is a two-stage single-arm, open-label, multi-centre hybrid trial of treatment with monoclonal anti-VAP-1 antibody, BTT1023, in adult patients with PSC. The sample size will be a maximum of 59 patients, who will each have up to 7 intravenous infusions of BTT1023 over a 78-day treatment period. All patients will be followed up until Day 120 (42 days after the last administration of treatment). At specified time points during each visit, serum will be taken for circulating levels of BTT1023 as well as for anti-drug antibodies, VAP-1 activity and additional exploratory research samples. This includes pre dose, during dose and post dose, with some patients also attending 24 hours later for further blood testing.

The trial is composed of two components. The run-in component of the trial incorporates a conventional 3+3 cohort design to confirm the therapeutic dose, with decisions regarding continuation based on toxicity and pharmacokinetic (PK) data, figure 1. The trial begins with the recruitment of 6 patients all receiving the starting dose of 8 mg/kg. Recruitment will be paused while awaiting the results of trough blood serum levels of circulating BTT1023 at Visit 7 (Day 50) from all 6 patients and until the dose-limiting toxicity (DLT) reporting period is completed for each patient (Visit 10 [Day 99]).

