**Figure 1 F1:**
[figure not shown]
Flow diagram showing the trial decision guidelines for the run-in period of the trial design, incorporating a conventional 3+3 cohort design if dose escalation is required.

If results from the first cohorts show an acceptable DLT rate (see later) and trough levels of BTT1023 meet the stipulated success criteria, the trial will continue into the expansion component of the trial. Acceptable trough levels have been set a trough concentration of 3 μg/mL free circulating BTT1023 at 8 weeks from first infusion, which is approximately 100-fold the dissociation constant (K_d_) of BTT1023 from VAP-1 and will result in target occupancy of approximately 90%. In the event that DLT rate is acceptable but the PK levels do not meet the success criteria, then the trial moves into a conventional 3+3 cohort design, using escalating doses of BTT1023. In this event, the original cohort of 6 patients will no longer be evaluated, but a new cohort of 3 patients will be recruited to receive the newly identified test dose of 12 mg/kg. If there are no DLTs at Visit 10 [Day 99], an additional cohort of 3 patients will be recruited at the new test dose. If the DLT rate remains acceptable but the PK levels still do not meet the success criteria, a further 3+3 patients will be recruited at the highest dose of 16 mg/kg. If this is found not to result in sufficient blood levels of BTT1023, then the trial will be stopped. If the PK values are found to be too high (such as resulting in trough levels consistently exceeding 100 μg/mL), then there is potential to de-escalate the dose in agreement with the Data Monitoring Committee (DMC) and after regulatory approvals. The trial will be stopped at any stage where patient safety is compromised. Individual patients will only receive one dose level. Once a confirmed dose has been established, the trial will expand until a total of 37 patients have received treatment with the confirmed dose, including those patients who have previously received this dose during the confirmatory period. Those patients not receiving the confirmed dose will not be included in the final evaluation.

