**Figure 2 F2:**
[figure not shown]
BUTEO trial schema.

A aliquot (0.5–1.0 mL) of the BTT1023 infusion solution will be taken at the end of every infusion and refrigerated. These samples may be used for analysis of BTT1023 concentration if anomalies in PK data are observed that could be due to errors in IMP preparation.

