### Data analysis plan

#### Power calculations and sample size justification

The dose confirmatory stage requires a maximum of 18 patients. The sample size has been based on the classic 3+3 design, investigating three fixed dose increments (8, 12 and 16 mg/kg), with no dose skipping.

The expansion phase follows a Simon’s two-stage minimax design with lower and upper acceptability bounds of 15% and 30%, respectively, and error rates α=0.10 and β=0.20. Thirty-seven patients are required in this stage of the trial; however, to account for patient dropout, estimated at approximately 10%, the sample size is extended by a further 4 patients. As such, the target recruitment is up to 41 patients for the expansion phase and up to 59 participants in total. An interim assessment will examine the primary outcome once 18 evaluable patients have been recruited at the confirmed dose. If 3 or more responses are observed in stage 1, then the trial will continue into stage 2. Recruitment will not be halted while stage 1 is assessed. If the stage 1 criterion is not met, then the trial will cease. However, if the criterion is met, then further patient recruitment continues until 37 evaluable patients are recruited. If overall there are 9 or more responses from 37 evaluable patients, then we conclude that the treatment warrants further investigation.

In this setting, the interpretation of alpha (α) is the probability satisfying stage 1 and observing 9 or more responses in 37 patients overall when the true response rate is 15%; a false-positive result (type 1 error). Beta (β) is the probability of failing to acknowledge activity when the true response rate is 30% (type 2 error). As such, the power, 1−β, is the probability of taking an effective treatment forward.

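### The printed vial strength, fixed 50 mL infusion volume and mg/kg doses cannot all be right: 50 mL holds at most 500 mg, a full 8 mg/kg dose only up to 62.5 kg

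*Protocol article*

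**What the plan says.** The product description (Protocol article, section BTT1023 (now known as Timolumab)) gives the presentation and the need for dilution: "BTT1023 is contained in single-use 100 mg/10 mL glass vials and requires dilution". It then says that the amount of diluent is "calculated to consistently provide a total diluted drug product infusion volume of 50 mL".

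Dosing is by body weight throughout:

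- Study design overview: "The trial begins with the recruitment of 6 patients all receiving the starting dose of 8 mg/kg".
- Text below Figure 1: if toxicity is acceptable but trough levels fall short, a new cohort receives 12 mg/kg. If levels still fall short, "a further 3+3 patients will be recruited at the highest dose of 16 mg/kg". After that: "If this is found not to result in sufficient blood levels of BTT1023, then the trial will be stopped".
- Power calculations and sample size justification: the run-in is described as "investigating three fixed dose increments (8, 12 and 16 mg/kg), with no dose skipping".

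The Patient selection section admits adults aged 18 to 75 and prints no weight limit, though its exclusion list is stated to be partial. No dose cap, second vial strength or exception to the 50 mL volume appears in the article.

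**The concern.** The diluent is whatever remains of 50 mL once the concentrate has been measured out. That works only while the concentrate takes up less than 50 mL. At the printed strength, the weight-based dose passes that point at ordinary adult weights, and the instruction then calls for a negative amount of diluent.

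This matters because dose level and measured trough drive the run-in. Failing the 3 μg/mL trough criterion moves the trial to 12 mg/kg, then to 16 mg/kg, then to a stop. If a site treated 50 mL as binding and cut the drug to fit, every patient above 62.5 kg would receive the same 500 mg at all three levels. The step from 12 to 16 mg/kg would then add no drug for anyone above 41.7 kg. A trough failure could reflect the volume of the infusion rather than the pharmacology of the dose. That outcome depends on how the text was applied, which the article does not show.

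**Working it through.** **Inputs from the article.** Vial: 100 mg in 10 mL. Total infusion volume after dilution: 50 mL. Doses: 8, 12 and 16 mg/kg. Body weights are not given, so 50, 70 and 100 kg are assumed for illustration.

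**Step 1: a case where the stated volume works.** At 8 mg/kg and 50 kg the dose is 8 × 50 = 400 mg. The concentrate needed is 400 / 10 = 40 mL, which leaves 10 mL of diluent and a total of 50 mL. Here the figures agree.

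**Step 2: the most drug that 50 mL can hold.** Strength = 100 / 10 = 10 mg/mL. With no diluent at all, 10 × 50 = 500 mg.

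**Step 3: weight limits.** Maximum weight = 500 / (dose per kg).

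| Dose | No diluent | 10% of volume is diluent (assumed) | Half of volume is diluent (assumed) |
|---|---|---|---|
| 8 mg/kg | 500/8 = 62.5 kg | 56.3 kg | 31.3 kg |
| 12 mg/kg | 500/12 = 41.7 kg | 37.5 kg | 20.8 kg |
| 16 mg/kg | 500/16 = 31.25 kg | 28.1 kg | 15.6 kg |

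The last two columns multiply the first by 0.9 and 0.5. Because dilution is required, the first column is an upper bound.

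**Step 4: concentrate needed before any diluent.** Volume = dose × weight / 10, that is 0.8, 1.2 or 1.6 mL per kg.

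| Assumed weight | 8 mg/kg | 12 mg/kg | 16 mg/kg |
|---|---|---|---|
| 50 kg | 40 mL | 60 mL | 80 mL |
| 70 kg | 56 mL | 84 mL | 112 mL |
| 100 kg | 80 mL | 120 mL | 160 mL |

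At 70 kg the diluent to add would be 50 − 56 = −6 mL, 50 − 84 = −34 mL and 50 − 112 = −62 mL.

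**Step 5: dose delivered if 50 mL were binding.** The most that could be given is 500/50 = 10.0, 500/70 = 7.1 and 500/100 = 5.0 mg/kg at 50, 70 and 100 kg. At 70 and 100 kg this falls below even the starting dose.

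**Step 6: what would reconcile the figures.** To fit a 100 kg patient into 50 mL, the strength would have to exceed 800/50 = 16, 1200/50 = 24 or 1600/50 = 32 mg/mL at the three levels. Doubling either the strength (20 mg/mL) or the volume (100 mL) gives 1000 mg, and undiluted limits of 125, 83.3 and 62.5 kg.

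**The case against.** The strongest reply accepts the arithmetic and disputes the consequence. In the quoted sentence, diluent is the quantity that is adjusted. Nothing says that drug is withheld to keep within 50 mL, and the dose is stated only in mg/kg. On that reading, a 70 kg patient at 8 mg/kg simply receives more than 50 mL, and only the volume statement is wrong. This stands: under-dosing is a possibility, not something the article shows.

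Second, expansion also requires an adequate measured trough, so the trial could not easily proceed at too low an exposure. That is fair. What remains is the risk of a needless escalation or a wrong stop, and only under the literal 50 mL reading.

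Third, an aliquot of each infusion is kept: "These samples may be used for analysis of BTT1023 concentration if anomalies in PK data are observed". This helps less than it seems. An aliquot gives concentration, and undiluted drug reads 10 mg/mL whether 50 mL (500 mg) or 56 mL (560 mg) was infused.

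Fourth, 12 and 16 mg/kg are used only if escalation occurs. At the starting dose, lighter patients fit and the assumed 70 kg patient is 6 mL over. This is correct, and it limits how much weight the larger figures should carry.

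Finally, a condensed article may have dropped a qualification held in the full protocol or pharmacy manual. That is possible, but the complaint is not of missing detail. The article prints three figures that conflict, and it says the volume holds *consistently*. A hidden weight limit would have to exclude adults above 62.5 kg at the starting dose, which is not plausible.

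**Conclusion.** The concern holds. As printed, the preparation rule cannot be carried out above 62.5, 41.7 and 31.25 kg at 8, 12 and 16 mg/kg, and the true limits are lower because dilution is required. These limits rest only on figures in the article; the patient weights and diluent fractions used to illustrate them are assumed. The fault may be a misprint of the strength or the volume, or a lost qualification.

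The effect on the trial is conditional. If the mg/kg dose was kept and 50 mL exceeded, trough levels and ALP response are unaffected. If 50 mL was kept, dose levels would merge for heavier patients and the run-in decisions would be unreliable. The interim and final response thresholds are not touched. This should be corrected, because it concerns the delivered dose and costs little to put right.

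**What to change.** 1. Check strength, volume and dose against the pharmacy manual and correct whichever is wrong.
2. If 10 mg/mL is right, replace the fixed 50 mL with a total volume set by dose level and body weight, exceeding 0.8, 1.2 or 1.6 mL/kg at 8, 12 or 16 mg/kg.
3. State that the mg/kg dose takes precedence over the infusion volume.
4. As an additional safeguard, before applying the 3 μg/mL criterion, confirm from vial counts and infused-volume records that each run-in patient received the full calculated dose in mg. If the retained aliquots are assayed, combine the concentration with the infused volume.

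The first three items are a text correction. The fourth is a records check on the run-in patients. Design, endpoint and decision rules do not change.

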### Objectives

The trial primary objective is to determine the activity of the anti-VAP-1 antibody BTT1023 in patients with PSC as measured by a decrease in alkaline phosphatase (ALP) levels (primary endpoint) with secondary endpoints to include various measures of liver injury and fibrosis and evaluation of the safety, effective dose and tolerability of BTT1023 in patients with PSC. Our secondary objectives include determining the mechanisms of action of BTT1023 through in vitro assessment of sVAP-1 concentration, SSAO enzyme activity and immune cell function; evaluating the potential of a novel MRI-based assessment of liver fibrosis and biliary strictures for assessing therapeutic response in PSC; and assessing the use of sVAP-1/SSAO as a biomarker to monitor disease progression in PSC.

## Methods

### Study design overview

BUTEO is a two-stage single-arm, open-label, multi-centre hybrid trial of treatment with monoclonal anti-VAP-1 antibody, BTT1023, in adult patients with PSC. The sample size will be a maximum of 59 patients, who will each have up to 7 intravenous infusions of BTT1023 over a 78-day treatment period. All patients will be followed up until Day 120 (42 days after the last administration of treatment). At specified time points during each visit, serum will be taken for circulating levels of BTT1023 as well as for anti-drug antibodies, VAP-1 activity and additional exploratory research samples. This includes pre dose, during dose and post dose, with some patients also attending 24 hours later for further blood testing.

The trial is composed of two components. The run-in component of the trial incorporates a conventional 3+3 cohort design to confirm the therapeutic dose, with decisions regarding continuation based on toxicity and pharmacokinetic (PK) data, figure 1. The trial begins with the recruitment of 6 patients all receiving the starting dose of 8 mg/kg. Recruitment will be paused while awaiting the results of trough blood serum levels of circulating BTT1023 at Visit 7 (Day 50) from all 6 patients and until the dose-limiting toxicity (DLT) reporting period is completed for each patient (Visit 10 [Day 99]).

